#### Recruitment strategies

2.2.5

Participant recruitment will take advantage of several strategies. Participants in this RCT will be mainly recruited from Shanghai Shuguang Hospital, Shanghai Ruijin Hospital, Shanghai Renji Hospital, and Shanghai Yueyang Hospital. Posters which will be put up in those 4 hospitals include brief introductions about the purpose, procedures, free treatments, possible risks of the trial, and researchers’ contact information. After screening test, another researcher will assign those participants who have signed the consent forms to different intervention groups. The recruitment process will be conducted by a clinical recruitment staff.

#### Randomization and allocation

2.2.6

A computer program (Strategic Applications Software [SAS], version 9.1.3 [SAS Institute Inc., Cary, NC]) will be used by a statistician to generate the random allocation sequence. Four hospitals will be chosen as strata by using a stratified block randomization scheme. Opaque envelopes will be used to seal generated sequences and delivered to each center. Having enrolled participants meeting the selection criteria, the researcher will open the random allocation envelope in front of each participant one by one and assign him to 1 of 3 groups.

### Blinding

2.3

This study will not be blinded.

### Interventions

2.4

The enrolled participants will be allocated into 3 groups: electroacupuncture (EA) group, manual acupuncture (MA) group, or western medicine group.

Participants in EA group and MA group will receive 12 sessions of acupuncture treatment for 4 weeks, 3 times a week by experienced acupuncturists to ensure identical acupuncture treatment according to the standard operating procedures using stainless steel disposable needles (Energy, 40 mm in length and 0.25 mm in diameter, Jiajian Medical Supplies Co Ltd, Jiangsu, China). The same acupoints will be selected for participants in these 2 acupuncture groups. After skin sterilization, acupuncturists will puncture DU20, DU24, and GB8 horizontally 8 mm into the scalp skin. LR3, LI4, GB20, LI11, KI3, GB34, ST36 will be punctured vertically 15 mm into the skin, and only PC6 will be punctured 8 mm into the skin vertically to keep off the median forearm nerve. Needle manipulation including lifting, thrusting, and rotating will be done to obtain needling sensation (de-qi sensation). Acupoints of DU20, DU24, and bilateral ST36 will be stimulated using an electric current at a frequency of 2/15 Hz by EA device (Hwato, SDZ-II, Suzhou Medical Supplies Co Ltd, Jiangsu, China) in EA group, whereas EA device will not be used in MA group. The needle retention time for both two acupuncture groups will be 30 minutes for each session.

Participants allocated to western medicine group will only take 20 mg fluoxetine orally per day for 4 weeks instead of receiving acupuncture treatment.

### Outcome

2.5

#### Primary outcome

2.5.1

The primary outcome of the clinical study will be the score changes of Hamilton Depression Scale (HAMD) between baseline, 4 weeks after EA treatment onset, and 6-month follow-up.

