### Sample size

2.7

The data statistician will be responsible for the calculation of the required sample size in each group. Based on previous studies, the cure effects of EA, MA and western medicine for depression were 15.7%, 17.4%, and 2.9%, respectively. Considering a significance level of 0.05 and a statistical power of 0.9, the calculated sample size in total is 120. Assuming about a 20% drop rate at a 1:1:1 allocation ratio, 144 participants will be recruited in this trial with 36 for each group.

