### Statistical analysis

2.9

SPSS 24.0 (SPSS Inc., Chicago, IL) will be used to conduct the whole data analysis. The intention-to-treat (ITT) analysis will include any participant who has at least one treatment session. The “last observation carried forward” rule will be applied to manage missing data in ITT analysis of secondary outcomes, whereas the maximum likelihood estimation method will be used for primary outcome. Any participant who receives at least 9 treatment sessions during the trial will be included in per protocol analysis.

Considering the homogeneity of the baseline characteristics between groups, group *t* test for quantitative data and Chi test for qualitative data will be applied. Group *t* test for normally distributed data or Mann-Whitney *U* test for non-normally distributed data will be used to compare variables between groups. For differences within each group, repeated measured analysis of variance will be used to analyze assessments of different time points, whereas Wilcoxon signed-rank test will be selected for non-normally distributed data. A *P* value <.05 will be considered statistically significant (2-sided).

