## Discussion

3

EA has been found to be effective in treating with depression with few side effects in a number of clinical studies,^[27–30]^ but an updated Cochrane review^[18]^ concluded that there was lack of solid evidence to recommend that EA is a beneficial treatment for depressive patients in many aspects due to poor quality of previous trials, which required further high-quality trials to support the recommendation. Besides, fluoxetine, as a selective serotonin reuptake inhibitor, is a widely used antidepressant. It was found to be effective in treating depression.^[31]^ This RCT is designed to compare the difference results of intervention by EA, MA, and fluoxetine to evaluate the efficacy of EA in treating depression and provide reliable clinical evidence.

The strengths of this RCT are associated with its multicentered design, concealed randomization, scales of multiple dimensions, imageological changes, specific biomarkers to better evaluating EA's efficacy. Based on the theory of TCM, the combination of acupoints DU20, DU24, GB8, LR3, LI4, GB20, LI11, KI3, GB34, ST36, and PC6, most frequently used for treating depression, can alleviate depressive symptoms by dispersing liver qi and relieving qi stagnation.

However, limitations in this trial should also be noted. It is unfeasible to blind the acupuncturists or clinicians who will treat participants from three groups differently. Meanwhile, participants allocated to different groups will definitely accept different treatments. Thus, participants cannot be blinded either. Double blinding is hard to be performed in this RCT.

As a conclusion, according to the CONSORT^[19]^ and STRICTA^[20]^ guidelines, the aim of this trial is to provide acupuncturists and clinicians with robust evidence of the efficacy and safety of EA treatment for depressive patients.

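### Two unranked primary time points and three arms compared by two-sample tests at an unadjusted P<.05: the primary HAMD analysis, read as written, does not hold a 5% error rate

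*Protocol article*

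**What the plan says.** Section 2.5.1 (Primary outcome) of the protocol article sets the primary outcome as "score changes of Hamilton Depression Scale (HAMD) between baseline, 4 weeks after EA treatment onset, and 6-month follow-up". There are two post-baseline times, and neither is marked as the main one. The abstract and section 2.8 repeat both times without ranking them.

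Section 2.4 (Interventions) fixes three arms: "The enrolled participants will be allocated into 3 groups: electroacupuncture (EA) group, manual acupuncture (MA) group, or western medicine group".

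Section 2.9 (Statistical analysis) names a group *t* test for normal data and otherwise a Mann-Whitney *U* "test for non-normally distributed data will be used to compare variables between groups". Repeated-measures analysis of variance appears there too, but only for changes within each group. One threshold covers everything: a P "value <.05 will be considered statistically significant (2-sided").

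No comparator is singled out. The Discussion states the purpose as to "compare the difference results of intervention by EA, MA, and fluoxetine to evaluate the efficacy of EA in treating depression". Section 2.7 lists planning rates for all three arms ("the cure effects of EA, MA and western medicine for depression were 15.7%, 17.4%, and 2.9%, respectively") and does not tie the calculation to one pair.

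**The concern.** Both named between-group tests compare two samples. With three arms they can only be applied pair by pair, which gives three contrasts. Two unranked times double that to six primary tests, four of which involve EA. Each is judged at .05, and the text provides no gate, order or correction.

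At stake is what a significant primary result would mean. A reader will take a reported P<.05 on the primary outcome as carrying a 5% false-positive risk. If several unranked tests can each count as that result, the risk for the set is higher, and the article does not say which comparison the trial's conclusion rests on.

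**Working it through.** **Inputs from the article.** Three arms (section 2.4); two post-baseline times (section 2.5.1); two-sample tests at two-sided 0.05 without adjustment (section 2.9).

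**Input not in the article.** The correlation r between a patient's HAMD change at week 4 and at 6 months. I take 0.3 to 0.7 as the working assumption and show 0 to 1 as the full range.

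**The plan's own figure.** The article states only a per-test level of 0.05 and no error rate for the set of primary tests. A single simulated contrast at a single time returns 5.0%, as it should.

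**Number of tests.** Pairs: 3 × 2 / 2 = 3. All primary tests: 3 pairs × 2 times = 6. Tests involving EA: 2 comparators × 2 times = 4.

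**Independence benchmark.** 1 − 0.95^6 = 26.5% for six tests and 1 − 0.95^4 = 18.5% for four. These are too high, because pairs share arms and the two times share patients.

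**With the correlations built in.** For arms i and j with equal size n, z = (mean_i − mean_j) / (σ√(2/n)). Two contrasts sharing an arm at the same time have correlation 0.5 in absolute value; the same contrast at the two times has correlation r. I simulated 400,000 replicates with all arms equal at both times and counted any |z| > 1.96:

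| r | One contrast, both times | Four EA tests | All six tests |
|---|---|---|---|
| 0 | 9.7% | 17.2% | 22.9% |
| 0.3 | 9.5% | 16.8% | 22.3% |
| 0.5 | 9.0% | 16.1% | 21.3% |
| 0.7 | 8.3% | 14.8% | 19.6% |
| 1 | 5.0% | 9.1% | 12.2% |

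Actual *t* tests at 36, 40 and 48 patients per arm give 19% to 22% for all six tests over r = 0.3 to 0.7, so the normal approximation is adequate.

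**Partial repairs.** Naming one time but keeping all three pairs at .05 leaves 12.2%; keeping only the two EA pairs leaves about 9%. Naming one contrast but keeping both times leaves 8.3% to 9.5% for r = 0.3 to 0.7. Both the contrast and the time have to be settled, or the threshold adjusted.

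**Full repairs.** One named contrast at one named time: 5%. Bonferroni over four tests: 0.05 / 4 = 0.0125 each, with simulated family-wise error 4.6% at r = 0.3 and 4.1% at r = 0.7. Bonferroni over six: 0.05 / 6 = 0.0083 each, giving 4.4% and about 4.0%. Neither can exceed 5% at any r, since 4 × 0.0125 = 6 × 0.0083 = 0.05 (up to rounding).

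**The case against.** *The analysis plan may settle this.* It is not shown, and an article may leave a testing order to it. That stands as far as it goes: a reader might infer that the sponsor is free to pick the time and contrast after seeing the data, and the article does not establish that. What is on the page is a primary outcome with two unranked times and a general threshold without adjustment. Following that text gives the inflated rate.

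*The article lists neither six tests nor a rule for declaring success.* True. The count is inferred from two-sample tests on three arms, though no other between-group test is offered.

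*About 20% counts the wrong set.* Largely fair. The aim concerns EA, and MA versus fluoxetine cannot support a claim for EA. The four-test figure of 15-17% is therefore the relevant one. It counts significant results in either direction; those favouring EA alone come to about 7.4-8.5% for r = 0.3 to 0.7, against 2.5% for one two-sided test. The inflation is smaller in absolute terms but about threefold.

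*Maximum likelihood for the primary outcome may signal a joint longitudinal model.* Section 2.9 introduces it as the way to handle missing data. Even as a joint model, it would not by itself choose a time or contrast or adjust the threshold.

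*Two further readings are tempting and unsupported.* One is that the planning rates of 15.7% and 17.4% show EA versus MA cannot be won. Those are cure rates, the primary outcome is a score change, and the one does not determine the other. The second is that the 6-month score reflects five months of other care. The article does not describe care after week 4, nor say whether the 6 months run from the start or the end of treatment.

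**Conclusion.** The point holds in this form: two unranked primary times and three arms, tested pairwise at an unadjusted two-sided .05, do not keep the primary HAMD analysis at 5%. Under equality of all arms at both times, the chance of at least one significant result is about 15-17% over the four EA tests and about 20-22% over all six pairwise tests.

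These sizes rest on equal arms and an assumed between-visit correlation of 0.3 to 0.7. Over all correlations from 0 to 1 they run from 9% to 17% and from 12% to 23%, so the conclusion does not depend on that assumption. A reader might take the 20% as the chance of a false claim for EA; it is not, because it includes MA versus fluoxetine.

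**What to change.** Amend the primary outcome and statistical analysis sections before any outcome data are seen, by one of two routes.

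1. **One primary test.** Name one contrast and one time at two-sided 0.05, for example EA versus fluoxetine on HAMD change to week 4. Test the other EA contrast and the other time in a stated fixed sequence, each only if the one before is significant. Report the remaining comparisons as secondary, with confidence intervals.
2. **Co-primary tests.** Keep both times and the EA contrasts as co-primary and adjust: Bonferroni at 0.0125 each for the four EA tests, or 0.0083 each if all six are to count.

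The choice is the sponsor's. The Introduction gives scarce follow-up assessment as a reason for the trial, so keeping 6 months as co-primary is defensible.

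The change is to wording only and needs no extra patients or visits. Under route 1, comparisons made secondary lose confirmatory status, and a later step in the sequence cannot be claimed if an earlier one fails. Under route 2, each test faces a stricter threshold and so has less power at the same sample size.

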##### HAMD

2.5.1.1

The HAMD is a doctor-rated questionnaire designed to assess depression severity by rating multiple dimensions including probing mood, feelings of guilt, suicide ideation, insomnia, agitation or retardation, anxiety, weight loss, and somatic symptoms with a score on a 3 or 5 point scale.^[22]^ Scored by the researcher, the scale can present objective and reflective results. A score of 0 to 7 is considered to be “normal,” whereas scores of ≥20 indicate “moderate or severe depression.” The assessment time is 20 minutes.^[23]^

#### Secondary outcomes

2.5.2

Secondary outcomes will be scored at the same time points as primary outcome, including Self-Rating Depression Scale (SDS), Depression Scale of traditional Chinese medicine (Depression Scale of TCM), brain fMRI, and blood biomarkers.

##### SDS

2.5.2.1

Designed to assess depression severity for patients diagnosed with depression,^[24]^ the SDS is a short self-rated questionnaire consisting of 30 items that rate the affective, psychological, and somatic symptoms associated with depression. Assessed by the patient, the results of the scale are comparatively direct and subjective. Each item is scored on a scale of 1∼4. Depression severity is classified into “normal” (score 20∼44), “mild” (score 45∼59), “moderate” (score 60∼69), and “severe” (score ≥70).^[25]^

##### Depression Scale of traditional Chinese medicine (TCM)

2.5.2.2

Based on the theory of TCM, the depression scale of TCM includes 6 items concerning depression-related symptoms such as chest distress, belching, palpitation, insomnia, fatigue, irritability, and weeping. Each item is scored on a 0∼3 scale. Higher summed scores indicate severer symptoms of depression from the perspective of TCM.

##### Brain fMRI

2.5.2.3

A General Electric (GE) signa 1.5T echo speed superconducting MRI scanner will be used to perform the fMRI measurements. Functional images will be acquired with an echo-planar imaging (EPI) sequence. During the resting-state fMRI acquisition, each participant will be required not to think of anything and keep their eyes closed without falling asleep for 4.5 minutes’ fMRI scanning. Statistical Parametric Mapping (SPM12), Resting-State fMRI Data Analysis Toolkit (REST), and Data Processing Assistant for Resting-State fMRI (DPARSF) will be used to conduct the preprocessing of fMRI data. First, the remaining images will be corrected for different slice acquisition timing and head motion. Second, the images will be spatially normalized to the standard EPI template in SPM12 and resampled to a voxel size of 3 × 3 × 3 mm^3^.Third, the images will be smoothed with an isotropic Gaussian kernel (FWHW = 4 mm) and temporal band-pass filtered (0.01–0.08 Hz). Finally, the Automated Anatomical Labeling (AAL) atlas will be used to segment brain signals.^[26]^ One hundred sixteen brain regions and 144 volumes will be obtained after preprocessing.

##### Blood biomarkers

2.5.2.4

Blood samples of participants will be collected and clot for at least 30 minutes at room temperature and centrifuged at 3000 rpm for 10 minutes at 4°C. Obtained serum samples will be stored at −80 °C until the day of enzyme-linked immunosorbent assay (ELISA) experiment. Serum 5-HT and BDNF will be measured using ELISA kits from R&D Systems (Minneapolis, MN). Serum NE and DA will be measured using ELISA kits from Weiao Co., Ltd. (Shanghai, China). Interleukin (IL)-6, TNF-α, and IL-1β levels in serum will be measured using ELISA kits from Xitang Co., Ltd. (Shanghai, China).

### Safety assessment

2.6

During the whole treatment, participants safety will be assessed to avoid adverse events (AEs). AEs of acupuncture mainly include local bleeding or pain, local redness or bruising, itching, and dizziness, whereas fluoxetine will bring about a series of AEs such as nausea, upset stomach, constipation, headaches, insomnia. A researcher will record the time of occurrence, severity, progress and treatment of AEs at each visit. Once any severe AE occurs, both the principal investigator and the institutional review board (IRB) will be informed and take prompt actions simultaneously.

### Sample size

2.7

The data statistician will be responsible for the calculation of the required sample size in each group. Based on previous studies, the cure effects of EA, MA and western medicine for depression were 15.7%, 17.4%, and 2.9%, respectively. Considering a significance level of 0.05 and a statistical power of 0.9, the calculated sample size in total is 120. Assuming about a 20% drop rate at a 1:1:1 allocation ratio, 144 participants will be recruited in this trial with 36 for each group.

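### The stated 90% power with 120 patients does not follow from the stated cure percentages, and a cure-proportion calculation does not support power for the HAMD score-change primary outcome

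*Protocol article*

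**What the plan says.** All quotes are from the protocol article.

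- **Sample size (2.7), effect inputs:** "the cure effects of EA, MA and western medicine for depression were 15.7%, 17.4%, and 2.9%, respectively". The section does not define cure effect and names neither a test nor a comparison.
- **Sample size, result:** "Considering a significance level of 0.05 and a statistical power of 0.9, the calculated sample size in total is 120". At equal allocation this is 40 per arm.
- **Sample size, recruitment:** the dropout and allocation assumption reads "Assuming about a 20% drop rate at a 1:1:1 allocation ratio", and the target that the section draws from it is "144 participants will be recruited in this trial with 36 for each group".
- **Section 2.5.1, definition of the main endpoint:** "The primary outcome of the clinical study will be the score changes of Hamilton Depression Scale (HAMD) between baseline, 4 weeks after EA treatment onset". A third assessment follows at six months. This is a continuous score. No cure proportion appears among the primary or secondary outcomes.
- **Statistical analysis (2.9):** groups are compared by t test, or by Mann-Whitney U test if the data are not normal, with this threshold: "A *P* value <.05 will be considered statistically significant (2-sided)".

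**The concern.** The section prints what a comparison of proportions needs (three percentages, a significance level, a target power and an allocation ratio) and then a total. A reader can therefore test the total against the inputs, and it falls far short.

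There is a second problem. The inputs look like the proportion of patients cured, but the trial will analyse change in HAMD score. Power for one endpoint does not carry over to another, and the section gives no HAMD difference or SD.

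The 0.9 figure is the only power statement in the article. The trial is presented as a high-quality answer to a literature judged to be of very low quality. If its results are later weighed against a 90% power claim that neither the inputs nor the endpoint supports, the precision of the comparison will be misjudged.

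**Working it through.** **Inputs.** From Sample size: p = 0.157 (EA), 0.174 (MA), 0.029 (fluoxetine); alpha 0.05; power 0.90; total 120, so n = 120/3 = 40 per arm. From Statistical analysis: two-sided. Assumption: cure effects are proportions of patients cured.

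**1. Attempt to reproduce 120 with a three-group chi-square test (2 df).**
- Mean p = (0.157 + 0.174 + 0.029)/3 = 0.120, and p(1 − p) = 0.1056.
- Sum of squared deviations = 0.037² + 0.054² + 0.091² = 0.012566.
- Noncentrality = n × 0.012566/0.1056 = 0.1190n. At n = 40 it is 4.76, giving power 48.3%.
- Power reaches 90% at n = 106.3, so 107 per arm (321 in total).

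**2. Pairwise comparisons, pooled-variance formula.**
n = [1.960 √(2p̄(1 − p̄)) + 1.282 √(p₁(1 − p₁) + p₂(1 − p₂))]² / (p₁ − p₂)²
- EA vs fluoxetine: p̄ = 0.093 and the difference is 0.128. n = [(1.960 × 0.4107 + 1.282 × 0.4006)/0.128]² = 106.1, so 107 per arm. Power at 40 per arm is about 50%.
- MA vs fluoxetine: p̄ = 0.1015 and the difference is 0.145. n = [(1.960 × 0.4271 + 1.282 × 0.4146)/0.145]² = 89.1, so 90 per arm. Power at 40 per arm is about 58%.

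**3. Does another method rescue 90%?** Only 40 × 0.029 = 1.2 cures are expected on fluoxetine, so large-sample formulas are rough here. Other methods at 40 per arm:

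| Method | Three-group | EA vs fluoxetine | MA vs fluoxetine |
|---|---|---|---|
| Large-sample, two-sided | 48% | 50% | 58% |
| Simulated, uncorrected chi-square (200,000 runs) | 52% | 57% | 65% |
| Simulated, Fisher exact | – | 33% | 43% |
| Large-sample, one-sided | – | 63% | 70% |

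Pooling both acupuncture arms against fluoxetine (80 vs 40) gives 60.5%. Across pooled, unpooled, arcsine and continuity-corrected formulas, one- and two-sided, the smallest three-arm total for 90% power in a pairwise comparison with fluoxetine is 192 (64 per arm; one-sided arcsine, MA vs fluoxetine). None gives 120.

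**4. If the percentages are changes in score.** The power then depends on an SD, which is not stated, so 120 cannot be reproduced.

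**5. What the design can detect on a continuous score.** For a two-arm t test at two-sided 0.05 and 90% power, the approximate detectable difference is (1.960 + 1.282) × √(2/n) SD. The noncentral t gives slightly larger values:

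| Evaluable per arm | Where the number comes from | Detectable difference |
|---|---|---|
| 40 | 120/3 | 0.73 SD |
| 38 | 144 × 0.8 = 115.2, over 3 arms | about 0.75 SD |
| 29 | 36 × 0.8 = 28.8 | about 0.87 SD |

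The last two rows differ because the section contradicts itself: 36 × 3 = 108, whereas 144/3 = 48.

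**The case against.** The strongest reply is that cure effect is undefined. If the figures are mean percentage improvements, they would suit a score-change outcome, and 120 could be right. A three-group ANOVA with means of 15.7, 17.4 and 2.9 and 40 per arm has 90% power if the SD is about 19.7 points (92% at 19, 89% at 20). That SD is assumed, and a condensed article may leave it to the full protocol.

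Part of this stands. The shortfall to 33–70% is conditional on the proportion reading, and it cannot be said with certainty how the 120 was obtained. But the alternative needs a figure the article does not give, so it shows only that some SD would fit. It does not support the stated 0.9.

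Three stronger readings are tempting, and the article does not support them:

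- **That the trial is underpowered for HAMD change, or needs 321 patients.** The 107 per arm belongs to a cure proportion, which is not an outcome here. Without a HAMD difference and SD, power for the primary outcome is unknown, not shown to be low.
- **That true power is 48–50%.** Those figures belong to one test family and two of the possible comparisons, and the section names no test.
- **That the section claims power for EA over MA and fails.** The inputs put MA above EA, and about 10,000 per arm would be needed to separate them, but no power is claimed for that comparison.

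**Conclusion.** The point holds. Read as proportions, the section's own inputs give roughly one half to three fifths power by the usual two-sided formulas, and about 33% to 70% across the exact and one-sided variants tried, against the 90% stated. The per-arm number would have to be about 2.7 times larger (107/40) for the three-group test or EA vs fluoxetine, and 2.25 times (90/40) for MA vs fluoxetine. Read as score changes, the figure cannot be verified.

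The endpoint mismatch follows from the proportion reading but not from any choice of test. A cure-proportion calculation says nothing about power for a t test or Mann-Whitney test on HAMD change. Under either reading, the article does not support the 0.9 power claim for its primary analysis.

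The conclusion assumes equal allocation, two-sided 0.05 and 40 analysed per arm, all taken from the article.

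**What to change.** Remove the cure-rate justification and the 0.9 power claim from the Sample size section. Restate it for HAMD score change, on the contrast and time point the sponsor names as primary. The article designates neither, and this point does not choose them. Give either an assumed mean difference and SD with the resulting power, or the detectable difference at the evaluable number.

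Before quoting a detectable difference, reconcile 36 per group with 144 in total (48 per group), since the value depends on it: about 0.75 SD at 38 evaluable per arm, or about 0.87 SD at 29. The 0.73 SD at 40 per arm should be used only if 40 evaluable per arm is really expected. Neither recruitment figure gives that after 20% dropout, because 120/0.8 = 150, not 144.

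If the percentages were in fact score improvements, say so and state the SD used.

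The cost is a rewritten paragraph and a less favourable stated power or detectable effect. No extra patients are needed.

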**Methods/Design::**

A 3-arm parallel, nonblinded, randomized controlled trial will be performed in 4 hospitals (centers). A total of 144 participants will be divided into 3 groups: EA group, manual acupuncture (MA) group, and western medicine group. Participants in EA group and MA group will receive 12 sessions of acupuncture treatment for 4 weeks. Participants allocated to western medicine group will only take 20 mg fluoxetine orally per day for 4 weeks. The primary outcome is Hamilton Depression Scale. Secondary outcomes are Self-Rating Depression Scale, Depression Scale of traditional Chinese medicine (Depression Scale of Traditional Chinese Medicine), brain fMRI and blood biomarkers including neurotransmitters serotonin, dopamine, noradrenaline, inflammatory cytokines inerleukin (IL)-1β, tumor necrosis factor-α, IL-6, and neurotrophin BDNF. All the outcomes will be assessed at baseline, 4 weeks after EA treatment onset and 6-month follow-up.

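### Sample size: 144 participants in three equal groups is 48 per group, not 36, and 144 does not leave 120 after a 20% loss

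*Protocol article*

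**What the plan says.** The Sample size section (2.7) gives the base requirement as follows: "Considering a significance level of 0.05 and a statistical power of 0.9, the calculated sample size in total is 120". It then allows for losses and sets the recruitment target: "Assuming about a 20% drop rate at a 1:1:1 allocation ratio, 144 participants will be recruited in this trial with 36 for each group".

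The Methods/Design part of the abstract gives the same total and the same number of arms: "A total of 144 participants will be divided into 3 groups: EA group, manual acupuncture (MA) group, and western medicine group". The Interventions section (2.4) also lists three groups. The trial runs in four centres; the abstract describes it as "nonblinded, randomized controlled trial will be performed in 4 hospitals (centers". Nowhere does the article mention a fourth arm or unequal allocation.

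**The concern.** A total, a number of equal arms and a size per arm are tied together: any two fix the third. Here all three are stated and they disagree. In addition, the step from 120 to 144 looks like multiplication by 1.2, which is not the inflation that a 20% loss requires.

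The group size is an operational number. Under Randomization and allocation (2.2.6), a statistician generates sequences stratified by hospital, and these are sealed in envelopes and sent to the centres. Someone preparing those lists from section 2.7 could reasonably produce 108 allocations or 144. At 36 per group the trial could not reach 40 analysable participants per arm even with no losses, so the power claimed in the same section would be out of reach from the start.

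**Working it through.** **Inputs**, all from the protocol article:
- Arms: 3, equal allocation (abstract; sections 2.4 and 2.7)
- Calculated total before losses: 120, so 120 / 3 = 40 per arm (section 2.7)
- Drop-out: about 20% (section 2.7)
- Recruitment target: 144 in total, 36 per group (section 2.7)
- Centres: 4 (abstract)

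**Group size**
- 3 × 36 = 108, not 144.
- 144 / 3 = 48 per arm.
- 144 / 4 = 36. The stated figure matches the total divided by the number of hospitals. That is a plausible origin, but the article does not say so.

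**Drop-out allowance**
- Reproducing the plan's figure: 120 × (1 + 0.20) = 144.
- Recruitment needed to retain 120: 120 / (1 − 0.20) = 150, or 50 per arm.
- Retained from 144 at 20% loss: 144 × 0.80 = 115.2, or 38.4 per arm. The shortfall is 4.8, and 4.8 / 120 = 4%.
- Loss at which 144 leaves exactly 120: 1 − 120 / 144 = 16.7%.

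Because the article says *about* 20%, a range is useful:

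| Loss | Retained from 144 | Needed to retain 120 |
|---|---|---|
| 15% | 122.4 | 141.2 |
| 16.7% | 120.0 | 144.0 |
| 18% | 118.1 | 146.3 |
| 20% | 115.2 | 150.0 |
| 22% | 112.3 | 153.8 |

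**If 36 per group were carried out**
- Randomised: 108, which is 144 − 108 = 36 fewer than the stated total and 12 fewer than 120.
- Retained at 20% loss: 108 × 0.80 = 86.4, or 28.8 per arm. The shortfall is 33.6, and 33.6 / 120 = 28%.

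**What this does to power (conditional illustration)**

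The article gives no mean difference or standard deviation. I therefore took its claim of 90% power at 40 per arm as given and solved for the standardised difference that a two-sample t test would detect at two-sided 0.05. That difference is d = 0.734, which is an assumption derived from the claim and not a figure in the article.

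| Per arm | Power at d = 0.734 |
|---|---|
| 40 (the base claim) | 90.0% |
| 38.4 (48 per arm, 20% loss) | 88.8% |
| 28.8 (36 per arm, 20% loss) | 78.1% |

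These values show relative loss only. They are not estimates of this trial's actual power.

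**The case against.** - **The slip is obvious.** The total of 144 appears in both the abstract and section 2.7, and equal allocation is stated, so 36 is the outlier. No list length or per-arm target is given under Randomization and allocation, so nothing shows that the lists were built on 36. This is fair: a trial stopping at 108 is a risk, not an established fact. But section 2.7 is the only place that gives a group size, the number there is wrong, and a reader cannot tell which figure the lists follow.
- **The drop-out point is small.** The word *about* leaves room, 144 is exact at 16.7% loss, and on the illustration above power falls only from 90.0% to 88.8%. This stands. On its own the point would be minor; it is raised because the same sentence has to be rewritten.
- **Participants who drop out are not necessarily lost from the analysis.** The Statistical analysis section (2.9) includes anyone with at least one session and uses maximum likelihood for the primary outcome. So 115 and 86 are counts after a 20% loss, not fixed analysis-set sizes. The Elimination criteria (2.2.4) pull the other way by removing data after randomisation, so the analysed number cannot be settled from the text. The plan's own inflation nevertheless treats drop-outs as lost, and on that basis it falls short.
- **The power figures rest on a back-solved effect.** This is true, and they are labelled accordingly.

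None of these objections reconciles 36 per group with 144 in three equal groups.

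**Conclusion.** The point holds. The group size of 36 contradicts both the total of 144 and the 1:1:1 ratio in its own sentence; the value consistent with them is 48. This part needs no assumption and must be corrected. Carried out literally, 36 per group means 108 randomised and about 86 retained at 20% loss, 28% below the calculated 120.

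The drop-out allowance is also arithmetically wrong, but by little: about 115 retained instead of 120, a 4% shortfall, and none if losses stay at or below 16.7%. This assumes that drop-outs contribute nothing to the analysis.

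One limit should be clear. All of this takes "the calculated sample size in total is 120" as given. Reading the stated rates ("the cure effects of EA, MA and western medicine for depression were 15.7%, 17.4%, and 2.9%, respectively") as proportions, a two-sided 0.05 comparison of EA with western medicine at 90% power needs 107 per arm, so 120 was not reproduced. That is a separate question, and correcting 36 to 48 does not answer it.

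**What to change.** In section 2.7:
1. Replace 36 with 48 participants per group.
2. Confirm that the randomisation lists and envelopes sent to the four hospitals total 144, with 48 per arm. If 36 was meant as a per-hospital number, say so separately, and only if the sponsor confirms it. With equal recruitment across centres it would correspond to 36 / 3 = 12 per arm per hospital.
3. Restate the drop-out allowance in one of two ways: 144 allows for 16.7% loss, or a 20% loss leaves about 115 participants (38.4 per arm). Give the power at the number chosen, on a stated effect and test. Recruiting 150 (50 per arm) would also resolve it, but is not needed to make the text correct.

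The cost is one rewritten sentence and one check of the lists. Options 1 to 3 without the increase to 150 enrol no additional participants; the stated drop-out allowance becomes slightly less favourable. If the lists turn out to hold 36 per arm, they would have to be extended before recruitment closes.
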